#### Secondary outcomes

Psychological distress will also be assessed at 7 and 18 weeks to evaluate the short and intermediate impact of the intervention (Table 2). Whereas experiences of violence (type-specific violence and severity/high-intensity violence) will be assessed at 18 weeks and at 12 months. Each type of violence will be analysed as a separate binary outcome based on whether the participants report any act within the category. Severity or high-intensity violence will be assessed using established criteria [58], which classify several physical acts, repeated less-severe acts, frequent emotional or controlling acts, multiple emotional or controlling acts occurring once or a few times, and all sexual violence as indicators of high-intensity violence.

**Table 2 Tab2:** Description of secondary outcome measures, measurement tools, scoring, and time of measurement

Outcome	Measurement tool	Description and domains	Scoring	Time points*
Psychological distress	GHQ-12	Psychological distress over the past 2 weeks (anxiety, depression, and social dysfunction symptoms)	4-point Likert; bimodal scoring (0–0–1–1); total score 0–12	7 weeks, 18 weeks
Experience of physical violence	Modified Women’s Health Questionnaire**	Slapping, pushing, hair pulling, hitting, kicking, dragging, choking/burning, or threat/use of weapon	Binary (1 = any act; 0 = none)	18 weeks, 12 months
Experience of sexual violence	Modified Women’s Health Questionnaire	Forced sex, degrading/humiliating sexual acts or sex due to fear	Binary (1 = any act; 0 = none)	18 weeks, 12 months
Experience of psychological violence	Modified Women’s Health Questionnaire	Insults, belittling, humiliation, intimidation, or threats to harm participant or someone they care about	Binary (1 = any act; 0 = none)	18 weeks, 12 months
Experience of controlling behaviours (partner or family)	Modified Women’s Health Questionnaire	Restricting the participant’s social contact, surveillance, jealousy, restricting healthcare access, or blocking income-generating activities	Binary (1 = any act; 0 = none)	18 weeks, 12 months
Experience of severe/high-intensity violence	Modified Women’s Health Questionnaire	1 = Yes if participant reports ≥ 1 severe physical act, OR ≥ 2 less-severe physical acts, OR ≥ 1 emotional/controlling act “many times,” OR ≥ 3 different emotional/controlling acts “once/few times,” OR ≥ 1 sexual violence act. 0 = No if none of these criteria are met	Binary (1 = high-intensity; 0 = not high-intensity)	18 weeks, 12 months
PTSD symptoms	PTSD Checklist for DSM-5 (PCL-5)	20-item self-report of PTSD symptoms in past week	5-point Likert (0–4: 'not at all' to 'extremely'); total score 0–80	7 weeks, 12 months
Daily functioning	WHODAS 2.0, 12-item	Six domains of functioning (cognition, mobility, self-care, getting along, life activities, participation) in past 30 days	5-point Likert ('no difficulty' to 'extreme difficulty/cannot do'); total score 0–48	18 weeks, 12 months
Self-esteem	Modified Collective Self-Esteem Scale	16 items related to current attitudes, feelings, perceptions about belonging to the LGBTIQA + community	7-point Likert ('strongly disagree' to 'strongly agree'); total score 16–112	18 weeks, 12 months
Self-compassion	Self-Compassion Scale—Short Form	12 items related to current self-kindness, self-judgment, common humanity, isolation, mindfulness	5-point Likert scale ('almost never' to 'almost always'); total score 12–60	18 weeks, 12 months
Perceived social support	Modified Social Support Survey	5 items related to availability of emotional, informational, tangible, affectionate, and positive social interaction support in past 4 weeks	5-point Likert scale ('none of the time' to 'all of the time'); total score calculated as mean or sum, 5–25	12 months
Use of personal safety strategies	Modified Safety Planning Checklist	Use of practical safety measures (safe place, essential items, emergency plan, contact list) in response to potential violence	Binary (yes/no) for each item; descriptive summaries	18 weeks, 12 months
Use of community resources	Modified Women’s Health Questionnaire	Use of violence prevention/support resources reported at follow-up assessments	yes/no;	18 weeks, 12 months
Satisfaction with community resources	Modified Women’s Health Questionnaire	Satisfaction level with violence prevention/support resources reported at follow-up assessments	5-point Likert ('not satisfied at all' to 'very satisfied')	18 weeks, 12 months
Psychological outcomes profile	PSYCHLOPS	Psychological distress across problem severity, functioning and well-being over the past week	6-point Likert scale, each item scored 0–5; total score 0–20; plus, qualitative responses	7 weeks, 18 weeks

*PTSD* Post-traumatic stress disorder; *PCL-5* Post-traumatic Stress Disorder Checklist for DSM-5, *DSM-5* Diagnostic and Statistical Manual of Mental Disorders, Fifth Edition, *WHODAS 2.0* WHO Disability Assessment Schedule 2.0, *PSYCHLOPS* Psychological Outcome Profiles

^*^When multiple time points are listed for an outcome, each time point represents a distinct secondary outcome and will be analyzed separately

^**^Modified WHO Multi-country Study Questionnaire on Women’s Health and Domestic Violence

Post-traumatic stress disorder (PTSD) symptoms will be measured using the PTSD Checklist for DSM-5 (PCL-5) [59], a 20-item self-report instrument. It assesses the presence and severity of PTSD symptoms experienced during the past week, rated on a 5-point Likert scale ranging from ‘not at all’ to ‘extremely’. Total scores range from 0 to 80, with higher scores indicating greater PTSD symptom severity. PCL-5 scores will be measured at 7 weeks and 12 months.

Daily functioning will be assessed using the WHO Disability Assessment Schedule (WHODAS 2.0, a 12-item version) [60], which measures functional impairment across six domains (cognition, mobility, self-care, getting along with people, life activities, and participation in society) over the past 30 days. Responses are rated on a 5-point Likert scale ranging from ‘no difficulty’ to ‘extreme difficulty/cannot do’. Total scores range from 0 to 48, with higher scores indicating greater functional impairment. WHODAS scores will be assessed at 18 weeks and 12 months after baseline.

Self-esteem will be measured using the Modified Collective Self-Esteem Scale [61], which assesses participants’ attitudes, feelings, and perceptions regarding their belonging to the LGBTIQA + community. The 16-item scale uses a 7-point Likert response format ranging from ‘strongly disagree’ to ‘strongly agree’. Total scores range from 16 to 112, with higher scores reflecting more positive evaluation of, and stronger identification with, the group. Self-esteem will be measured at 18 weeks and at 12 months.

Self-compassion will be assessed using Neff’s Self-Compassion Scale—short form [62]. This 12-item measure evaluates components including self-kindness, self-judgement, common humanity, isolation, and mindfulness. Items are rated on a 5-point Likert scale ranging from ‘almost never’ to ‘almost always’, producing a total score from 12 to 60, with higher scores indicating greater self-compassion. Self-compassion scores will be assessed at 18 weeks and at 12 months.

Perceived social support will be assessed using the Modified Social Support Survey 5-item version (MSSS-5), which evaluates the availability of various types of support, including emotional/informational, tangible, affectionate, and positive social interaction, during the past 4 weeks. Responses are provided on a 5-point Likert scale ranging from ‘none of the time’ to ‘all the time’, producing a final score between 5 and 25, where higher scores indicate greater social support. The assessment will be made at 12 months.

Personal safety strategies will be measured using a Modified Safety Planning Checklist, which assesses participants’ use of personal safety measures in response to potential violence. Items cover practical activities such as securing a safe place to stay, keeping essential documents or items (e.g. medicines, cash, pair of extra clothes), preparing an emergency safety plan, and maintaining an emergency contact list. The outcome will be analysed as total checklist scores at 18 weeks and at 12 months after baseline, with higher scores indicating more safety strategies used.

Use and satisfaction with community resources for violence prevention and support will also be assessed. Use will be measured as a binary variable (yes/no to any use of services), and satisfaction will be measured on a 5-point Likert scale ranging from ‘not satisfied at all’ to ‘very satisfied’.

The Psychological Outcomes Profile (PSYCHLOPS) [32, 63] of the participants will be assessed using a self-reported measure designed to capture progress from the participants’ perspective by evaluating four questions related to problems, functioning, and well-being. Responses are provided both as free text narratives and on an ordinal six-point scale. Each question is scored from 0 to 5, producing a maximum total score of 20. The tool also includes an item assessing suicidal thoughts. Follow-up assessments will be made at 7 weeks and at 18 weeks after baseline assessments. Follow-up assessments using PSYCHLOPS will also include a question on participants’ current overall perception of change, rated from ‘feeling much better’ to ‘feeling much worse’, compared with their state prior to participating in the SAATHI intervention.

The information about outcome measures is summarized in Tables 1 and 2.

### Harms

The following harms will be monitored for this trial: increased psychological distress, worsening of existing mental health symptoms, new or intensified suicidal ideation, heightened fear or anxiety, and increased exposure to violence associated with participation in the intervention or research procedures. Studies have shown that there are no observed increases in serious adverse events, such as an increase in suicidal thoughts, associated with PM + when it is delivered by trained and supervised non-specialist helpers [31]. However, PM + will not be offered to high-risk individuals such as those with severe mental disorders or those at heightened risk of suicide, as the PM + is designed to address mild to moderate psychological distress.

Some safety strategies, including disclosure to informal networks or seeking help from formal institutions, may involve risks in certain contexts [64]. These risks can include escalation of violence or retaliation when involving others due to conflicts with the norms of family privacy, particularly when institutional support responses are ineffective. Evidence also indicates that safety planning may be of limited value where access to psychosocial services, housing assistance, and legal protection is constrained, which can leave survivors at continued risk [65]. Ensuring the availability of adequate support services is therefore necessary when promoting safety planning strategies.

As part of the individual counselling and the group sessions, participants will be invited to share and reflect on adversities, as well as explore possible solutions. This process may lead to increased psychological stress or emotional discomfort. Harms will be monitored systematically using tools such as PSYCHLOPS suicidal ideation item during counselling sessions or at follow-up assessments. Any adverse events will be documented using a standardized adverse event reporting form. Any serious events (suicide attempts, hospitalization for mental health reasons, escalation in the risk of violence, or any event that poses substantial danger to the participant) will be reported to the Data and Safety Monitoring Board for review and guidance.

This protocol is designed to safeguard all SAATHI participants. In cases of suicide risk, the study team will provide immediate referral to a mental health specialist, with the participants’ agreement, or link them to local support services in situations of risk of interpersonal violence.

There is also a potential risk of psychological distress or emotional exhaustion among peer advocates. This may arise from repetitive exposure to traumatic experiences shared by participants, as well as the peer advocates’ own daily challenges in a highly stigmatized environment. To reduce this risk, peer advocates will receive structured support. This will include regular debriefing sessions with mental health professionals, limits on the participants they work with each day, scheduled self-care breaks between sessions, and training in mindfulness and slow breathing techniques. In cases where peer advocates’ personal well-being is affected, individual counselling support will be made available. Burnout assessment will also be included in routine monitoring visits.

### Participant timeline

Figure 1 demonstrates the sequential steps of the SAATHI trial, beginning from screening and enrolment, followed by intervention delivery and subsequent follow-up assessments. Follow-up assessments will be conducted at baseline, and at 7 weeks, 18 weeks, and 12 months after baseline for all study arms. The schedule of enrolment, interventions, and assessments is outlined in Table 3.

**Fig. 1 Fig1:**
[figure not shown]
Schedule of enrolment, intervention delivery, and follow-up visits across study arms

**Table 3 Tab3:** Schedule of enrollment, interventions, and assessments

	Trial period					
Timepoint	Enrollment (-t1)	Allocation (0)	Intervention period (weeks 1–6)	7 weeks	18 weeks	12 months
Enrollment						
Outreach/Invitation	X					
Eligibility screen	X					
Informed consent	X					
Baseline Assessment		X				
Allocation/Randomization		X				
Interventions						
EUC		X				
SAATHI-I		X	X			
SAATHI-IG*		X	X	X	X	X
Assessments (Quantitative)						
Demographics/baseline characteristics	X	X				
Psychological distress						X
Experience of violence						X
Secondary outcomes**				X	X	X
Adherence/fidelity/safety						
Attendance tracking (individual + group sessions)			X			
Intervention fidelity checks (session, checklist; observation/debriefing)						X
Adverse event monitoring/referral if needed	X	X	X	X	X	X
Process evaluation (Qualitative)						
Interviews with participants and peer advocates			X	X	X	X

-t1 (enrolment): screening/consent prior to baseline assessment; 0 (Allocation): baseline assessment and randomization

^*^Group sessions begin after individual sessions and continue through follow-up period)

^**^Details of assessment time points for secondary outcomes are provided in Table 2

### Sample size

The SAATHI trial will enrol at least 960 participants (320 per arm). This sample size is estimated to provide 90% power to detect a standardized mean difference of 0.27 in psychological distress between the EUC arm and the SAATHI-I arm and between the SAATHI-I arm and the SAATHI-IG arm at 12 months after enrolment. Other parameters used in the sample size calculation include a standard deviation of 2.6 units [66], a two-sided α of 0.05, and a maximum assumed attrition rate of 10%. This standardized effect corresponds to an absolute mean difference of approximately 0.7 points on the GHQ-12 bimodal scale. The assumed effect size is conservative and is consistent with the range of effects reported in previous evaluations of PM + [67, 68] and with methodological work on clinically relevant effect size for psychotherapy [69].

This sample size is also sufficient to detect a 25% reduction in the proportion of participants reporting exposure to violence after receiving the PM + counselling (from 60% in the control arm to 45% in the SAATHI-I arm) at 12 months, with at least 90% power. To ensure adequate power for the planned secondary outcomes, the final planned enrolment was increased to at least 354 participants per arm (total *N* = 1062).

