The peer advocates who deliver the sessions are advised not to conduct more than four sessions per day to prevent emotional burnout. Additionally, they are encouraged to take a 30-min break between sessions to rest. Peer advocates will receive a monthly salary for their role as helpers in the study.

Participants who are allocated to the SAATHI individual plus group (SAATHI-IG) arm will also be invited to attend monthly group meetings (6–10 participants in each group) to strengthen social support. These group meetings will tentatively run for 60 to 90 min. During the sessions, participants can share their experiences with the SAATHI strategies (see Supplementary file 2), discuss the benefits and challenges of applying them in their daily life, and offer peer support. The group sessions aim to help participants maintain strategies that reduce psychological stress.

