### Data analysis

The quantitative analysis of effectiveness will be based on intention-to-treat with pairwise comparisons of the three arms. Descriptive statistics such as the mean, standard deviation, median, and range will be presented for continuous variables. The intervention effects on outcomes will be assessed using mean differences for continuous outcomes and risk ratios (RRs) and absolute risk differences for binary variables. Data will be analysed using STATA/SE version 15 (StataCorp LLC, College Station, TX).

Efforts will be made to minimize missing data. Primary analyses will be based on complete case analysis. To evaluate the robustness of our findings, we will perform sensitivity analysis using inverse probability weighting.

For analysis of secondary outcomes at 7 and 18 weeks, participants in the SAATHI-I and SAATHI-IG arms will be combined and considered as a single intervention group since the participants in the latter arm will not have completed the monthly group meetings, which extend to 11 months.

We will also conduct subgroup analyses to examine differential effects of the intervention by sexual identity (gay men vs. transgender women).

The qualitative analysis of data from the formative research and process evaluation will be based on reflexive thematic analysis, grounded in a critical realist/contextualist ontology where interviewees’ experiences are understood as lived realities that are produced and exist within broader social contexts [72–74]. The transcribed material will be managed in QSR NVIVO 13. We will conduct a reflexive thematic analysis focusing on phenomenological descriptions and narrative constructions through the following steps: (1) The interviewers note their immediate impressions and responses after the interviews to increase reflexive awareness of interpersonal processes in the interview situation. (2) Researchers read the transcribed material and the interviewers’ notes to obtain a basic sense of the interviewees’ experiences and how they give meaning to the intervention and associated processes. (3) Meaning units will be coded and the codes merged into themes. The themes will then be reviewed by the research team and refined to ensure that they capture the range of perspectives represented in the data. A second researcher will independently audit the thematic structure. The final themes will be synthesized into written text.

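### The 90% power for psychological distress assumes independent outcomes, although the SAATHI arms are clustered by peer advocate and, in SAATHI-IG, by group

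*Protocol article*

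**What the plan says.** The Sample size section sets 320 participants per arm and states: "This sample size is estimated to provide 90% power to detect a standardized mean difference of 0.27 in psychological distress". This applies to EUC vs SAATHI-I and to SAATHI-I vs SAATHI-IG at 12 months. The listed inputs are "a standard deviation of 2.6 units [66], a two-sided α of 0.05, and a maximum assumed attrition rate of 10" per cent, and the effect is described as an "absolute mean difference of approximately 0.7 points on the GHQ-12 bimodal scale". No ICC, design effect, caseload or group size appears. The same section covers violence ("from 60% in the control arm to 45% in the SAATHI-I arm", at least 90% power). It then raises enrolment to 354 per arm and gives power for secondary outcomes as the reason.

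The section on intervention structure, delivery and providers describes six weekly individual sessions delivered by peer advocates in both SAATHI arms. SAATHI-IG participants are also invited to "monthly group meetings (6–10 participants in each group) to strengthen social support". Data analysis says these meetings extend to 11 months.

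On the analysis, the article plans pairwise intention-to-treat comparisons and adds: "The intervention effects on outcomes will be assessed using mean differences for continuous outcomes and risk ratios", together with absolute risk differences for binary outcomes. It names no regression model and no variance estimator.

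**The concern.** Participants are randomised individually, but treatment is delivered through shared providers and shared groups. Outcomes of clients who see the same advocate, or sit in the same group, can be correlated. The article itself gives reasons to expect this:

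- It scores competency for each advocate (Process evaluation) and reviews session duration for each advocate (Monitoring of fidelity and adherence), so advocates are expected to differ.
- Participants may choose, after randomisation, a helper of the same or a different gender or sexual orientation. This can sort similar clients to the same advocate.
- The groups are meant to work through shared experience and mutual support, so dependence within a group is part of the intended mechanism.

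EUC offers information and referral without the six sessions or the groups, so clustering is unequal across arms. Positive correlation increases the variance of the arm mean. The stated power is then too high and, if the analysis had no term for clustering, confidence intervals would be too narrow.

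**Working it through.** **Reproducing the stated figure.** Inputs from Sample size: standardised difference 0.27 (0.7/2.6 = 0.269), two-sided α 0.05, power 90%, attrition 10%.

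- n per arm = 2 × (1.960 + 1.282)² / 0.27² = 288.3 analysable.
- 288/0.9 = 320 enrolled.

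So 320 is the figure for independent observations, with no allowance for clustering. At 354 enrolled, about 318 are analysable (354 × 0.9 = 318.6), and power under independence is 0.926.

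**Adding clustering.** Assumptions not in the documents: 20 advocates in the arm, equal caseloads, ICC 0.01–0.05. Groups of 8 lie inside the stated 6–10.

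- Design effect in an arm: DE = 1 + (m − 1) × ICC, where m is the cluster size.
- Average over the two compared arms: f = (DE₁ + DE₂)/2.
- Power = Φ(0.27 × √(n/(2f)) − 1.96).
- Type I error of a test that ignores clustering = 2 × (1 − Φ(1.96/√f)).

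*EUC vs SAATHI-I, clustering in the SAATHI-I arm only.* m = 288/20 = 14.4, or 318/20 = 15.9. Example at ICC 0.02 and n = 288: DE = 1 + 13.4 × 0.02 = 1.268, f = 1.134, power = Φ(0.27 × √(288/2.268) − 1.96) = Φ(1.08) = 0.86.

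| ICC | f at 288 | Power, 320 enrolled | f at 318 | Power, 354 enrolled | Type I error if ignored (288 / 318) |
|---|---|---|---|---|---|
| 0.01 | 1.067 | 0.88 | 1.075 | 0.91 | 5.8% / 5.9% |
| 0.02 | 1.134 | 0.86 | 1.149 | 0.89 | 6.6% / 6.7% |
| 0.05 | 1.335 | 0.80 | 1.373 | 0.83 | 9.0% / 9.4% |

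*SAATHI-I vs SAATHI-IG, group clustering in SAATHI-IG only, m = 8.*

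| ICC | f | Power, 320 enrolled | Power, 354 enrolled | Type I error if ignored |
|---|---|---|---|---|
| 0.01 | 1.035 | 0.89 | 0.92 | 5.4% |
| 0.05 | 1.175 | 0.85 | 0.88 | 7.1% |

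For groups of 6 to 10 at ICC 0.05, power is 0.86–0.83 at 320 enrolled and 0.89–0.87 at 354.

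If the two SAATHI arms used different advocates, advocate clustering would add to this. With group ICC 0.05, advocate ICC 0.02 and 20 advocates in each arm, f is 1.443 at 288 and 1.473 at 318, and power is 0.77 and 0.80.

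**Break-even.** 354 per arm keeps 90% power while f ≤ 318/288.3 = 1.10.

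**Violence, 60% vs 45%.** With the pooled-variance formula:

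- Required n = (1.960 × √(2 × 0.525 × 0.475) + 1.282 × √(0.6 × 0.4 + 0.45 × 0.55))² / 0.15² = 231 per arm, against 288 analysable even at 320 enrolled (power 0.95).
- At 354 enrolled, 20 advocates and ICC 0.05, the effective n is 318/1.373 = 232 per arm, so power is about 0.90.

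**The case against.** The strongest reply has four parts.

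1. **The analysis is not stated to be unclustered.** A reader might infer that standard errors will be too small. The article does not support that. It gives comparisons and effect measures but no model, and a mean difference or risk ratio can come from a mixed model or with cluster-robust errors. Data Availability mentions an analysis plan, which is not shown. The type I error figures are therefore conditional. The power figure is different: it is stated with its inputs, and a later analysis plan cannot change what it assumed.

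2. **The trial now enrols 354 per arm.** A reader might infer that the design no longer has 90% power for either comparison. That does not follow. At ICC 0.01, power at 354 is 0.91 with 20 advocates and 0.92 with groups of 8. The shortfall at 354 depends on the ICC. The increase was, however, justified by secondary outcomes and not by clustering.

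3. **The key inputs are assumed.** This stands. Process evaluation plans interviews with approximately 20 peer advocates, but that is a qualitative sample governed by saturation and not a count of the workforce. EUC also has trained peer advocates. Whether they create clustering in that arm is not stated; if they do, power for EUC vs SAATHI-I is lower still.

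4. **The ranking of the comparisons is open.** A reader might infer that SAATHI-I vs SAATHI-IG suffers most because SAATHI-IG has two levels of clustering. That holds only if the two arms use different advocates. The article describes one training covering both packages. If advocates are shared, their effect largely cancels in that contrast, and group clustering alone costs less (0.88 against 0.83 for EUC vs SAATHI-I, at ICC 0.05 and 354 enrolled).

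**Conclusion.** The concern holds as a defect in the stated power. The 90% for GHQ-12 at 320 per arm rests on independence, which the described delivery does not support, and any positive ICC puts power below 90% at that size. At the final 354 per arm the loss ranges from none to moderate over ICC 0.01–0.05: 0.91 to 0.83 for EUC vs SAATHI-I (20 advocates in the arm) and 0.92 to 0.88 for SAATHI-I vs SAATHI-IG (groups of 8, group clustering only). The violence outcome is less affected, at about 0.90 in the least favourable of the 20-advocate scenarios at 354.

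These are normal-approximation figures with equal cluster sizes. The number of advocates and the ICC are assumptions. An inflated type I error, about 5.4–9.4% in the two tables, would follow only if the comparisons were run without a clustering term. The documents do not settle whether they will be.

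**What to change.** In the Sample size section, replace the single 90% with power at 354 per arm for each of the two comparisons, over a stated range of ICC, advocate caseload and group size. Say whether the same advocates serve both SAATHI arms.

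In Data analysis or the analysis plan, specify a partially nested model for the primary analyses, with an advocate effect in the arms where advocates deliver care and a group effect in SAATHI-IG. For the binary violence outcome, cluster-robust standard errors with a small-sample correction would serve. Attach advocate and group identifiers to each participant record; the session registers and attendance records the article describes should supply them.

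The cost is wording, two identifier variables, a lower stated power and slightly wider intervals. No added enrolment is needed. Recruitment stood at 1054 of 1062 on 29 December 2025, no interim analysis of outcomes is planned and final follow-up runs to January 2027, so the model can still be fixed before the final analysis.
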